**Fig. 1 Fig1:**
[figure not shown]
Participant timeline. Abbreviations: BPT: bouldering psychotherapy; CBT: cognitive behavioural therapy; EP: exercise program; EQ-5D: EuroQol Five Dimension Questionnaire; FERUS: Questionnaire on Resources and Self-Management Skills; FKB-20: Body Image Questionnaire; GAD-7: Generalized Anxiety Disorder 7; GSE: General Self-Efficacy Scale; MADRS: Montgomery-Asberg Depression Rating Scale; PHQ-9: 9-Item Patient Health Questionnaire; R-SES: Rosenberg Self-Esteem Scale; SCL-90: Symptom-Checklist; SD: Standard Deviation; VAS: visual analogue scale.

**Table 1 Tab1:** Trial Registration Data

Data category	Information
1. Primary registry and trial identification number	ISRCTN12457760
2. Date of registration in primary registry	26 July 2017
3. Secondary identifying numbers	–
4. Source(s) of monetary or material support	OH-DO-KWAN Stiftung [name] und [name] Förderverein Kletterzentrum Aufwärts in Miesbach e.V.
5. Primary sponsor	OH-DO-KWAN Stiftung [name] und [name]
6. Secondary sponsor(s)	Förderverein Kletterzentrum Aufwärts in Miesbach e.V.
7. Contact for public queries	see Point 8
8. Contact for scientific queries	PD [name], [contact]
9. Public title	Study KuS (Klettern und Stimmung - Climbing and Mood), a combination of bouldering and psychotherapy for treating depression
10. Scientific title	Study KuS (Klettern und Stimmung - Climbing and Mood) - Prospective investigation of the effectiveness of a combination of bouldering and psychotherapy in comparison with an active control group and cognitive behavioural group therapy for patients suffering from depression in an outpatient setting
11. Countries of recruitment	Germany
12. Health condition(s) or problem(s) studied	Depression
13. Intervention(s)	Study arm 1: Intervention group receiving the combination of bouldering and psychotherapy
	Study arm 2: Intervention group receiving cognitive-behavioural therapy
	Study arm 3: Active control group
1.14. Key inclusion and exclusion criteria	Ages eligible for study: adults; Sexes eligible for study: both
	Inclusion criteria: 1. Depression, measured by the patient’s score on the PHQ-9 (Cut-off ≥8) 2. Informed consent to participate in the study (especially regarding randomised allocation and data acquisition) 3. Ability to come to the therapy locations
	Exclusion criteria: 1. Acute suicidality 2. Severe psychiatric disorder (psychosis, mania, substance abuse) 3. Physical contraindication for climbing due to disorder or pregnancy 4. BMI < 17.5 or > 40 5. Age < 18 years 6. Actual participation in group psychotherapy 8. Began using psychiatric medication within the last 8 weeks 9. Began psychotherapy within the last 8 weeks 10. Planned inpatient stay during therapy
15. Study type	Randomised controlled intervention study
16. Date of first enrollment	June 2017
17. Target sample size	199
18. Recruitment status	complete
19. Primary outcome(s)	Depression measured using the score on an observer rating scale (Montgomery Asberg Rating Scale, MADRS) by computer-assisted telephone interviews (CATI)
20. Key secondary outcomes	e.g., body image, anxiety, social phobia, self-esteem, coping

### Sample size estimation

A power analysis was computed on the basis of the authors’ previous experience with the BPT in the pilot study in which a Cohen’s d of 0.77 was reached [33]. To address Hypothesis I, a slightly lower effect size of 0.6 was assumed. Thus,61 patients will be needed in the BPT group and 61 patients in the EP group (alpha = .05, power = .9).

To address Hypothesis II, a non-inferiority margin of 1.9 points (SD = 3.8) on the PHQ-9 (as proposed in the literature [36]) was used, which resulted in a total of 69 patients in the BPT group and 69 patients in the CBT group (alpha = .05, power = .9). Thus, there should be 61 patients in the EP group, 69 patients in the BPT group, and 69 patients in the CBT group, for a total of 199 patients. To account for dropouts between t0 and t1, 20% more patients are added (based on the drop-out-rate of our pilot study), resulting in 40 additional patients for a total of 239.

Therefore, 10 waves in three therapy centres (two waves in Berlin, four waves in Weyarn, four waves in Erlangen) were planned. Each wave was designed to include 24 participants on average, of which 20 were expected to complete the respective intervention.

Also from the data of the pilot study, in which similar recruitment modalities were applied, a failure of approx. 40% of patients who do not meet the inclusion criteria must be expected. This means that a total of approximately 400 patients should be screened.

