### Data analysis

The data analyses will be performed with the “IBM SPSS Statistics 21” software. In order to be able to assess the quality of the randomisation, the baseline data from the intervention and control groups will be examined for statistically significant differences. All data will be checked for plausibility. Patients who drop out of the study but are still available for the telephone interviews are being interviewed subsequently. A missing data evaluation will be carried out, and missing values will be imputed by EM-Imputation [62]. The main outcome criterion is severity of depression assessed by the MADRS. The primary data analytic strategy is “per protocol” for the superiority trial and “intention to treat” for the non-inferiority trial [63]. As a sensitivity analysis, an additional analysis with “intention to treat” for hypothesis 1 and “per protocol” for hypothesis 2 will be performed. The level of statistical significance is set at *p* = 0.05.

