#### Hypothesis 2: non-inferiority of BPT to CBT

The second hypothesis will be tested by conducting a non-inferiority analysis with both measurements for depression, the PHQ-9, and the MADRS. The reason for this is that a predefined equivalence margin for the PHQ-9 already exists in literature, but this is not the case for the MADRS. For the PHQ-9, we will use the established equivalence margin of 1.9 points [36, 64]. For the MADRS, only two predefined equivalence margins can be found in the literature, both established for medical treatment against placebo and not for CBT as in our study [65, 66] .

Historical trials of cognitive behaviour group therapy have yielded effect sizes of Cohen’s d ranging from 0.4 [67] to 0.68 [68] to 1.3 [35]. The non-inferiority margin can be chosen as half of the mean difference between state-of-the-art therapy and the control treatment [63, 69, 70]. Because it is easier to find non-inferiority if the margin is larger, we will calculate it with the two lower margins of 0.2 (0.5*0.4) and 0.34 (0.5*0.68) from the two current meta-analyses. Therefore, we will calculate Cohen’s d / Hedges’ g of the between-group difference (BPT-CBT).

Furthermore, the difference between CBT and the active control group EP will be calculated, and the mean difference will be used as a supplementary non-inferiority margin as proposed by different authors [63, 69, 70], who suggest controlling for one’s own standard therapy by using an additional control group if historical trials for the estimation of the non-inferiority margin are missing. Because our EP group is designed as an active control group with a therapeutically active intervention (physical activity), the margin found in the comparison between CBT and EP is likely to be conservative compared to an inactive control group. Various authors [63, 69, 71] recommend the definition of the margin based on clinical considerations. At an average severity interval of about 10 points (below 10 points remission, 10 to 20 points mild depression, to 31 points moderate depression [44, 45]), a reduction of at least 5 points appears clinically relevant. The margin to be determined should therefore not exceed 5 points.

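### The 90% power stated for non-inferiority applies only to the PHQ-9 margin; on the MADRS, the main outcome, power is about 32% or 63%, and no deciding test is named

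*Protocol article*

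**What the plan says.** Under Sample size estimation, Hypothesis II is sized on "a non-inferiority margin of 1.9 points (SD = 3.8) on the PHQ-9", giving "69 patients in the BPT group and 69 patients in the CBT group (alpha = .05, power = .9". The level is not described as one-sided or two-sided. The planned total is "61 patients in the EP group, 69 patients in the BPT group, and 69 patients in the CBT group, for a total of 199 patients", and for dropout "20% more patients are added (based on the drop-out-rate of our pilot study), resulting in 40 additional patients for a total of 239".

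Under Data analysis: "The main outcome criterion is severity of depression assessed by the MADRS". The abstract and the registration table (Table 1) also give the MADRS alone as the primary outcome. The section on primary outcome measures describes both the MADRS and the PHQ-9.

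Under Hypothesis 2, the article plans on "conducting a non-inferiority analysis with both measurements for depression, the PHQ-9, and the MADRS". The PHQ-9 margin of 1.9 points is taken from the literature. For the MADRS, the article finds only margins set for medical treatment against placebo, and so turns to a general rule: "The non-inferiority margin can be chosen as half of the mean difference between state-of-the-art therapy and the control treatment". It cites effects of group CBT of d = 0.4, 0.68 and 1.3, and then says "we will calculate it with the two lower margins of 0.2 (0.5*0.4) and 0.34 (0.5*0.68) from the two current meta-analyses". It adds the observed CBT-EP difference as a supplementary margin, and a ceiling of 5 MADRS points.

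**The concern.** The sample size section gives one power figure for Hypothesis II, and that figure belongs to a margin and a scale other than those planned for the main outcome. A reader who takes the trial as 90% powered for non-inferiority would be wrong about the MADRS.

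The margins also differ widely in strictness. In SD units the PHQ-9 margin is 1.5 to 2.5 times the MADRS margins. If the two treatments are truly equal, the PHQ-9 test is likely to succeed, the MADRS test at 0.20 is likely to fail, and the one at 0.34 has roughly a one-in-three chance of failing. Mixed results are therefore foreseeable, and the article has no rule for what they would mean. What is at stake is whether a non-inferiority claim could rest on the loosest of several unranked margins, and whether an inconclusive MADRS result would be recognised as the expected outcome of low power.

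**Working it through.** **Inputs** (Sample size estimation; Hypothesis 2)
- PHQ-9 margin 1.9, SD 3.8
- alpha 0.05, power 0.90, 69 per arm
- MADRS margins d = 0.20 and 0.34
- 20% added for dropout: 69 × 1.2 = 82.8, about 83 randomised per arm
- Assumption: true difference 0 (the article states none)

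**Step 1: reproduce the stated sample size.** The standardised margin is 1.9 / 3.8 = 0.50.

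n per arm = 2 (z₁₋α + z₁₋β)² / d²

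- One-sided 5%: 2 × (1.645 + 1.282)² / 0.50² = 68.5, so 69. This matches. The noncentral t gives 70.
- One-sided 2.5%: 2 × (1.960 + 1.282)² / 0.50² = 84.1, so 85. This does not match.

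The stated 69 therefore implies one-sided 5%. The same formula at two-sided 5% for Hypothesis I (d = 0.6) gives 58.4, so 59. The t version gives 60, close to the stated 61; one-sided 5% gives 49 by t. The two calculations are written with the same alpha but appear to use it differently.

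**Step 2: power at the MADRS margins.**

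Power ≈ Φ(d √(n/2) − z₁₋α), with √(69/2) = 5.874

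- d = 0.20: Φ(1.175 − 1.645) = Φ(−0.470) = 31.9%
- d = 0.34: Φ(1.997 − 1.645) = Φ(0.352) = 63.8%
- d = 0.50: Φ(2.937 − 1.645) = Φ(1.292) = 90.2%

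The noncentral t gives slightly lower values, which are used from here on:

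| Margin (SD) | n = 69, one-sided 5% | n = 83, one-sided 5% | n = 69, one-sided 2.5% |
|---|---|---|---|
| 0.20 (MADRS) | 31.7% | 35.9% | 21.4% |
| 0.34 (MADRS) | 63.4% | 70.4% | 50.9% |
| 0.50 (PHQ-9) | 89.9% | 94.1% | 83.0% |

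The n = 83 column treats every imputed value as fully informative, so for this analysis it is an upper bound.

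**Step 3: size needed for 90% power** (formula of Step 1)
- d = 0.20: 429 per arm at one-sided 5%, 526 at 2.5%
- d = 0.34: 149 per arm at one-sided 5%, 182 at 2.5%

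**Step 4: compare the margins.** 0.50 / 0.34 = 1.5 and 0.50 / 0.20 = 2.5. The 0.5 SD margin is above the smallest cited group-CBT effect (0.4) and below the other two (0.68 and 1.3). This comparison assumes that SD units carry over from the cited studies and between the two scales.

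**The case against.** The sample size section says openly that its calculation is on the PHQ-9. That scale is described among the primary outcome measures, and no sentence claims 90% power for the MADRS. This stands: the figure is not miscalculated. But it is the only power given for Hypothesis II, and it does not cover the outcome that the article calls its main one.

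The non-inferiority analysis is planned by intention to treat with imputation, so more than 69 per arm may contribute. Even the upper bound is only about 36% and 70%. Baseline adjustment could also help, though none is stated for Hypothesis II. With an assumed baseline correlation of 0.5 and 69 per arm, each margin is divided by √0.75, and power is about 38% and 74%.

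The 5-point MADRS ceiling might seem to supply the missing power. No MADRS SD is given. If it were 8, 10 or 12 (assumed), 69 per arm would give about 98%, 90% or 79% at one-sided 5% for a 5-point margin. But the article sets 5 points as a limit on the margin, not as the margin.

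A reader might infer four stronger things, which the document does not support:
- **That the PHQ-9 margin gives away the whole CBT effect.** It exceeds only the smallest of the three group-CBT effects. The Background also cites 0.55 to 0.98 for CBT.
- **That the PHQ-9 margin breaks the article's own rule.** The half-effect rule is offered as one that can be used, and it is applied to the MADRS. The PHQ-9 margin rests on a different, literature basis that cannot be checked here.
- **That mixed results would be read in favour of BPT.** Nothing says so. The choice of the two lower margins and the ceiling point towards caution.
- **That 61 per arm for Hypothesis I confirms a two-sided level.** It is only close to the computed 60.

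**Conclusion.** The point holds. The stated 90% power describes the PHQ-9 test at 0.5 SD and one-sided 5%. For the MADRS margins that the article itself sets, power is about 32% and 63%, and it stays well below 90% under every variation of sample count, level or adjustment tried above. The figures assume no true difference between BPT and CBT; a true deficit would lower them, and a true advantage would raise them. The article also fixes several margins on two scales without ranking them, so it does not define what would establish Hypothesis II. This is more than detail left to an analysis plan: the margins are set here, and the one power figure given does not belong to the main outcome.

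**What to change.** Before analysis, name one deciding test for Hypothesis II: the MADRS at t1, with the one-sided confidence bound for the BPT-CBT difference compared with one prespecified margin, 0.20 or 0.34. The choice between them is the sponsor's and should be justified in the text. In place of 90%, give that test's actual power, about 32% or 63% at one-sided 5% with 69 per arm, together with its assumptions. State the one-sided level explicitly; at 2.5% these become about 21% and 51%, and the PHQ-9 figure becomes 83%. Label the PHQ-9 result at 1.9 points, the MADRS margin not chosen and the CBT-EP margin as supportive, and keep the 5-point figure as a ceiling only.

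Table 1 lists recruitment as complete, so this changes wording and disclosure and adds no patients. The cost is a less favourable stated power and an open acknowledgement that the deciding test may well be inconclusive.

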### Recruitment strategies

Subjects are being recruited in several ways: Informational material (e.g. flyer, posters) is being distributed throughout the three study locations at psychiatric hospitals, locally based psychotherapist offices, primary care physician offices, pharmacies, and other psychological services (e.g. support groups). Information is also being sent to psychotherapists, psychiatrists, and primary care physicians requesting them to share it with their patients. Prior to each interventional wave, press releases are being issued and addressed to different local newspapers and radio stations, and presentations are being given at local events (e.g. “Day of Action against Depression”). On the web, a homepage (http://www.psychiatrie.uk-erlangen.de/med-psychologie-soziologie/klettern-und-stimmung-die-studie-kus/) and a Facebook account were created and are being updated with current information regarding the study on a regular basis.

### Eligibility of participants

All individuals interested in the study are being invited to attend information sessions held by the study personnel, where they are provided with all relevant information about the conditions surrounding their participation in the study (e.g. randomisation). People who are willing to participate are asked to fill out a short screening questionnaire (scanning for inclusion and exclusion criteria) and to provide their written informed consent.

#### Inclusion and exclusion criteria

To increase external validity, only a few inclusion and exclusion criteria are being applied. *Inclusion criteria* consist of acute depressive symptoms, informed consent to participate in the study (especially regarding randomised allocation and data acquisition), and the ability to reach the therapy locations. The presence (or absence) of depression is operationalised as a PHQ-9 score of at least 8 points, ensuring a high level of sensitivity to all depressive disorders [37]. *Exclusion criteria* are age younger than under 18 years, a Body Mass index (BMI) under 17.5 or over 40, contemporary participation in another psychotherapeutic group therapy, started taking psychiatric medication within the last 8 weeks (medication started before 8 weeks is not a reason for exclusion), started individual psychotherapy within the last 8 weeks (same as for medication), a planned inpatient stay during the intervention period, physical contraindication for bouldering (physical disorders or pregnancy), specific psychiatric disorders (psychosis within the last 5 years, a manic episode within the last 5 years, substance addiction with substance abuse within the last year, Borderline diagnosis with self-harming behaviour during the last year), and acute suicidality. If it turns out that someone is in a suicidal crisis, appropriate steps following good clinical practice and a suicide risk management plan should be taken by the study personnel, if necessary by arranging for inpatient admission. For safety reasons, all participants are obliged to sign an anti-suicide contract for the duration of the study. All inclusion and exclusion criteria are assessed via self-reports with the screening questionnaire. In cases of unclear fulfilment of the inclusion or exclusion criteria (especially regarding relevant psychiatric diagnoses), potential participants are personally interviewed by the study personnel.

### Randomisation

All individuals meeting the inclusion criteria in one study region are being randomised into one of the three groups (BPT, CBT, EP). Randomisation is stratified by sex and severity of depression according to the PHQ-9 score from the screening questionnaire (9–14 mild, 15–19 moderate, 20–27 severe depression). After randomisation, participants are informed about their allocation and provided with all necessary information about group participation. Randomisation is performed with a computer-based system by the Institute of Medical Informatics, Biometrics, and Epidemiology (IMBE) of the Friedrich-Alexander-Universität Erlangen-Nürnberg.

#### Masking

Participants know which treatment condition they are in, but the interviewers who conduct the CATIs and thus assess the outcomes of the study are blinded to participants’ allocations. Prior to each interview, all participants are reminded of the confidential nature of their allocation and asked not to tell the interviewer which treatment they receive.

### Interventions

#### Bouldering psychotherapy (BPT)

Bouldering is defined as climbing to moderate heights (up to around three metres) without the use of ropes or harnesses. The great variety of difficulty levels in bouldering gyms (usually marked by different colours) allows patients with different physical fitness levels to easily boulder together in one group without feeling over- or unchallenged. Our newly developed bouldering intervention is a combination of bouldering and psychotherapy and consists of 10 consecutive sessions of 2 hours, taking place in a bouldering gym once a week in the late afternoon. The intervention takes place in a group of about 10 patients who are supervised by two climbing therapists. We have teams of two therapists in each study region, but the compositions of personnel may vary across the different waves of therapy because the therapists are also balancing other commitments. All in all, we engage nine climbing therapists for the BPT groups. All but one of the climbing therapists are either psychotherapists or are in the process of completing their psychotherapy hours (psychotherapists must have a master degree in psychology plus an additional 4200 h of further education as a psychotherapist according to German law; the one exception has an Master of Science in Health Science including sports psychology) and are experienced in bouldering and rock climbing (their climbing ability is rated at a minimum of grade 7 on the UIAA (Union Internationale des Associations d’Alpinisme) scale; one person on each team had received advanced training from the German Alpine Association or the Austrian Institute for therapeutic climbing). Prior to the intervention, all of the therapists are thoroughly trained in bouldering techniques, safety rules, and didactic elements by a professional bouldering instructor and in the implementation of the bouldering therapy manual by two members of the study’s headquarters, both of whom had obtained qualifications in “therapeutic climbing”.

Each of the 10 sessions focuses on a specific psychological topic that we consider to be relevant in the development and maintenance of depression. An overview of the specific subjects covered in the 10 therapeutic sessions is provided in Table 2.

**Table 2 Tab2:** Overview of the bouldering therapy sessions

Session	Topic
1	Introduction to bouldering and mindfulness
2	Physical feeling and the body’s centre of gravity
3	Healthy handling of limitations
4	Expectations and standards
5	Self-efficacy, achievements, and pride
6	Self-esteem
7	Fear and trust I
8	Fear and trust II
9	Social relationships
10	Problem solving, reflecting on lessons learned, and transferring them to daily life

To ensure a standardised implementation of the BPT in all of the three therapy centres, the therapists follow a BPT manual that includes a fixed schedule for each session. Each session consists of three main parts: introduction (about 20 min.), action phase (about 75 min.), and closure (about 25 min.). The introduction phase takes place in an enclosed room (e.g. the yoga room) and begins with a mindfulness exercise (e.g. breathing meditation) to focus the patients’ attention on the current moment, followed by the presentation of the topic of the session and a brief exchange of patients’ experiences and psychoeducation regarding the specific subject (e.g. function and body signals of anxiety). Afterwards, patients are split into two smaller groups, and from then on, each group is supervised by one therapist. The action phase takes place in the bouldering hall and consists of one to two subject-related bouldering exercises that are supposed to evoke underlying emotions (e.g. anxiety), unveil patients’ characteristic patterns (e.g. avoidance), and - with the support of the therapists - enable patients to engage in new experiences (e.g. exposition: bouldering blindfolded). The remaining time in the action phase is used for free bouldering, meaning that patients work on their individual “projects” while supported by the therapists. The closure phase takes part in the enclosed room where all of the patients are reunited to talk about their experiences during the bouldering exercises and to develop ideas about how to integrate the lessons they learned into their daily lives. Each session ends with a body-related relaxation exercise.

